### Analyses

Descriptive statistics (means ± SD, or median and interquartile ranges, as appropriate) will be used to describe the entire study sample with regard to demographics, physical measurements and baseline lab values. The analyses will be conducted according to the intention to treat principle. Multilevel analyses will be performed to adjust for the clustering of observations of participants receiving care from the same nurse practitioner, and for repeated measurements within one patient. Linear and logistic regression models will be used to examine the effect of the intervention on each of the outcome measurements. Differences in changes between groups will be calculated with 95% confidence intervals. If there are any relevant differences in baseline measurements between the two groups, we will adjust the outcome for these factors (i.e. age, gender, ethnicity, BMI at the start of study, level of education, depression, smoking, number of sessions attended). Separate analyses of effect modifiers (i.e. gender, age) will be performed in order to gain a better understanding as to who benefits most from the intervention. Separate analyses of effect modifiers and mediators will be conducted in order to gain a better understanding as to who benefits most from the intervention

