**Methods:**

12,000 inhabitants, 30-50 years of age living in several municipalities in the semi-rural region of West-Friesland will receive an invitation from their general practitioner (n = 13) to measure their own waist circumference with a tape measure. People with abdominal obesity (male waist ≥ 102 cm, female waist ≥ 88 cm) will be invited to participate in the second step of the screening which includes blood pressure, a blood sample and anthropometric measurements. T2DM and CVD risk scores will then be calculated according to the ARIC and the SCORE formulae, respectively. People with a score that indicates a high risk of developing T2DM and/or CVD will then be randomly assigned to the intervention group (n = 300) or the control group (n = 300).

Participants in the intervention group will follow a CBP aimed at modifying their dietary behavior, physical activity, and smoking behavior. The counseling methods that will be used are *motivational interviewing *(MI) and *problem solving treatment *(PST), which focus in particular on intrinsic motivation for change and self-management of problems of the participants. The CBP will be provided by trained nurse practitioners in the participant's general practice, and will consists of a maximum of six individual sessions of 30 minutes, followed by 3-monthly booster sessions by phone. Participants in the control group will receive brochures containing health guidelines regarding physical activity and diet, and how to stop smoking. The primary outcome measures will be changes in T2DM and CVD risk scores. Secondary outcome measures will be changes in lifestyle behavior and cost-effectiveness and cost-utility ratios. All relevant direct and indirect costs will be measured, and there will be a follow-up of 24 months.

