### Sample size

In a Dutch working population of overweight people (BMI ≥ 25), which consisted of both males and females, the standard deviation of the ARIC score was found to be 8.11 [45]. For a two-sided detection of a 5% between-group difference in cardiovascular risk score, standardized at 60 years of age, with an alpha of 0.05 and a power of 90%, in the present study 120 participants will be needed in the intervention group and 120 in the control group. Assuming that 40 participants per collaborating GP are recruited, and each participant is randomized independently, this is feasible. We expect a response of approximately 65% in the first step of the screening, 20% of which will meet the abdominal obesity criterion [46,47]. Of those who meet this criterion, we expect that at least 80% will be willing to participate in the second step and the RCT (Figure 1).

A multilevel analysis is performed to be able to adjust for the clustering of observations within practices. To be able to perform stratified and multivariable analyses, and taking loss to follow-up into account, larger numbers will be needed. A total of 600 (i.e. 300 in the intervention group and 300 in the control group) is expected to suffice.

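### Covariates enter the primary comparison of changes only if an undefined baseline difference is seen, and the listed factors omit the baseline score but include a post-randomisation one

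*Protocol article*

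**What the plan says.** The Abstract of the protocol article defines the primary outcomes as changes: "The primary outcome measures will be changes in T2DM and CVD risk scores". The Analyses section gives the effect measure on the same scale: "Differences in changes between groups will be calculated with 95% confidence intervals". It names the model class: "Multilevel analyses will be performed to adjust for the clustering of observations of participants receiving care from the same nurse practitioner, and for repeated measurements".

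On covariates, Analyses states a conditional rule: "If there are any relevant differences in baseline measurements between the two groups, we will adjust the outcome for these factors". The factors follow in brackets: "i.e. age, gender, ethnicity, BMI at the start of study, level of education, depression, smoking, number of sessions attended". Nothing there or elsewhere in the article defines a relevant difference. The baseline ARIC or SCORE value is not among the factors, although both scores are calculated for every participant before randomisation (Study population).

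**The concern.** Three things in this rule look wrong.

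- **The model depends on the data.** Whether the primary estimate is adjusted, and for what, is settled after baseline differences have been inspected, and relevance is left to judgement. Several primary estimates are therefore open for each score.
- **The most useful covariate is not named.** The baseline value of the outcome is usually its strongest predictor and is already collected. An unadjusted comparison of changes subtracts the whole baseline difference, although only part of it would persist to follow-up. The arm that starts higher by chance then appears to improve more.
- **One listed factor is not a baseline measurement.** Sessions attended are a consequence of allocation. Adjusting for them would sit badly with the intention-to-treat principle in the same section.

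At stake are the credibility of the primary estimate as pre-specified, some precision, and possibly removal of part of the treatment effect.

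**Working it through.** **Inputs from the article.** Sample size: SD 8.11 ("the standard deviation of the ARIC score was found to be 8.11"), a difference of 5 (read here as percentage points), two-sided alpha 0.05, power 90%, a stated need of 120 per arm, and 300 per arm planned. Study duration: measurements at baseline, 6, 12 and 24 months.

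**Assumed.** The correlation rho between baseline and follow-up score is not given, so 0.5 to 0.9 is shown. The formulas below take one follow-up and ignore clustering.

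**1. The plan's own figure.** n per arm = 2(1.960 + 1.282)² × (8.11/5)² = 2 × 10.51 × 2.631 = 55.3, so 56, not 120. With 120 per arm, power for a difference of 5 is 99.8%, and the difference detectable with 90% power is 3.39. The mismatch with 120 is a separate matter and nothing below depends on it. It does show that 300 per arm is ample for 5 points on this SD. The SD is for ARIC, whereas the difference is stated for the cardiovascular score, for which no SD is given.

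**2. Precision, equal variances at both times.** Var(change) = 2·SD²(1 − rho). Var(baseline-adjusted) = SD²(1 − rho²). Ratio adjusted/change = (1 + rho)/2. Half-width of the 95% CI = 1.96 × √variance × √(2/300).

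| rho | ratio | saving | half-width, change | half-width, adjusted |
|---|---|---|---|---|
| 0.5 | 0.75 | 25% | 1.30 | 1.12 |
| 0.6 | 0.80 | 20% | 1.16 | 1.04 |
| 0.7 | 0.85 | 15% | 1.01 | 0.93 |
| 0.8 | 0.90 | 10% | 0.82 | 0.78 |
| 0.9 | 0.95 | 5% | 0.58 | 0.57 |

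**3. Effect of selecting on the score.** Suppose selection cuts the baseline variance to a fraction k, with slope and residual variance unchanged. Var(change) is then SD²[(1 − rho²) + k(1 − rho)²], and the ratio becomes (1 + rho)/[(1 + rho) + k(1 − rho)]. For k = 0.36 (a normal score cut at its mean, an assumption):

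- rho 0.5: 1.5/1.68 = 0.89
- rho 0.7: 1.7/1.808 = 0.94
- rho 0.8: 1.8/1.872 = 0.96
- rho 0.9: 1.9/1.936 = 0.98

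The saving falls to about 2% to 11%. Entry requires 10% on either score (Study population), so each score is only partly truncated, and the truth should lie between the two sets of figures.

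**4. Over-correction.** Given a chance baseline difference d (intervention minus control), the expected difference in change is the true effect minus (1 − rho)d. The standard error of d is 8.11 × √(2/300) = 0.66. For an imbalance of two standard errors (1.32), the shift is 0.66 at rho 0.5, 0.40 at 0.7 and 0.13 at 0.9. Averaged over randomisations it is zero.

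**5. The trigger.** Seven listed factors are true baseline measurements. If they are screened at p < 0.05 and taken as independent, the chance of at least one flag is 1 − 0.95⁷ = 30%. At p < 0.10 it is 1 − 0.90⁷ = 52%. Both thresholds are assumed, because the article gives none.

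A simulation under no effect (300 per arm, 8,000 runs at each of rho 0.5, 0.7 and 0.8) compared unadjusted change, baseline adjustment, and baseline adjustment only if the baseline score differed at p < 0.05. The mechanical trigger gave a type I error of 4.5% to 5.2%. Taking the smaller of the two p-values gave about 7%. The two analyses disagreed on significance in 3% to 5% of runs.

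**6. Sessions attended.** Only the intervention arm is offered counselling sessions; controls receive written information and brochures (Intervention group; Control group). The count is presumably zero for every control, so it differs by design and would trip any imbalance rule. With it in the model, the group coefficient describes intervention participants extrapolated to no sessions, which is not the effect of being assigned to the programme.

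**The case against.** The article never says that the baseline score is excluded. The bracketed list can be read as extra factors rather than the full model. Regressing change on group plus baseline gives the same treatment estimate as regressing follow-up on group plus baseline, so the change wording is compatible with proper adjustment. A repeated-measures model with a common baseline mean would also adjust implicitly. Such detail often sits in a full protocol or analysis plan, which is not shown.

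This stands in part: the absence of baseline adjustment is inferred from the wording. But the conditional rule is stated outright, its list opens with i.e. and so reads as complete, and nothing says that the baseline means are constrained. A model with free group-by-time terms and complete data reproduces the unadjusted change comparison.

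The precision argument is also open to challenge. The correlation is unknown and could be high: the ARIC inputs include ethnicity, parental history and height, SCORE includes gender, and age is fixed at 60 in both. At rho 0.9 little is lost. This stands.

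A reader might infer that selecting people at the 10% threshold lowers the correlation and so enlarges the loss. Step 3 shows the reverse. A reader might also turn savings of 10% to 25% into 60 to 150 of the 600 participants. That range needs equal variances and stops at rho 0.8, and it suggests a shortage that the plan's own inputs do not show.

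**Conclusion.** The concern holds in a limited form. The adjustment rule is data-dependent and has no criterion, its list omits the baseline value of the outcome, and it includes a post-randomisation factor. These are features of the stated text, and pre-specification is the stronger ground.

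The efficiency gain from routine baseline adjustment is real but modest. It is about 5% to 25% of the variance for an assumed rho of 0.9 to 0.5 with equal variances, and less where selection has narrowed the baseline score.

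A reader might go further and infer bias, an inflated error rate or an underpowered trial. The documents do not support this. Under randomisation the unadjusted comparison of changes is unbiased. A mechanically applied trigger on the baseline score kept type I error near nominal, and the excess came only from free choice between analyses, which an undefined criterion permits. Power for 5 points is ample on the stated SD. The change should be made, but the design does not fail without it.

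**What to change.** For ARIC, SCORE and each behavioural outcome, pre-specify one primary model. It always includes the baseline value of that outcome and a short fixed list of baseline covariates (for example sex, age and baseline smoking), and it is reported whatever imbalance is observed. If a repeated-measures model is kept, state how the baseline enters: as a covariate, or through a common baseline mean. Delete the imbalance trigger. Remove the number of sessions attended from the adjustment list.

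The cost is wording only. The baseline scores and covariates are already collected, and neither the sample size nor the visit schedule changes.

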### Intervention

#### Intervention group

The participants in the intervention group will receive the CBP to increase their motivation and ability to change their dietary pattern, physical activity or smoking behavior. The CBP will be provided by nurse practitioners in the participating general practices, and will consist of a maximum of 6 individual 30-minute counseling sessions [37], followed by 3-monthly booster sessions by phone for a period of one year. The MI and PST counseling methods will be used. The counseling sessions are initially given on a weekly base, but after a few sessions the time between the sessions is extended to 2/3 weeks, followed by 3-monthly booster sessions by phone, to act as a reminder for the participants, to reinforce what they have learned, and to give them support and feedback.

One of the techniques that is used during MI is reflective listening, which is applied throughout the whole counseling process. A 'gap' between the participant's current behavior and the broader goals will be emphasized, cultivating motivation for lifestyle change. When the participant recognizes such discrepancies, a certain level of discontent arises that makes change more likely to occur. Discrepancies are emphasized after exploring the participant's views on their current and future behaviors. Rolling with resistance invites the participant to consider a new perspective, instead of having it imposed. Finally, self-efficacy, or the confidence to change a specific behavior under difficult circumstances, will be supported whenever possible because it is one of the best predictors of treatment outcome. After the MI counseling the participant is willing to change and it is time to strengthen the commitment to a plan for lifestyle change using PST. The nurse practitioner, together with the participant, will make an implementation plan concerning where, when and how the behavior changes will take place. This will be done in the following series of stages [38]: explanation of the intervention and its rationale, definition and breaking down of the problem, establishing achievable goals for problem-solving (achievable goals are SMART goals: Specific, Measurable, Achievable, Relevant, Timed), generating multiple possible solutions, evaluating and choosing the solution, implementing the preferred solution, and evaluating the outcome.

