#### Control group

The participants in the control group will receive written information about their risk of developing T2DM and CVD, and existing brochures containing health guidelines regarding physical activity, a healthy diet, and how to stop smoking.

Participants with a systolic blood pressure above 160 mmHg and/or hypercholesterolemia (> 8 mmol/L) will be referred to their GP for additional medication, but will remain in the study. Participants with a glucose value above 7.0 mmol/L (confirmed with a second blood sample) will also be referred to their GP and then excluded for participation.

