### Data-collection

#### Questionnaires

▪ Dietary behavior: An extended and modified version of the 8-item Food Frequency Questionnaire [39] will be used to measure the intake of fruit, vegetable, fiber, alcohol consumption and (un)saturated fat. Total energy intake can not be measured with this questionnaire.

▪ Physical activity behavior: The Short Questionnaire to Assess Health Enhancing Physical Activity (SQUASH) [40] will be used to assess physical activity within (A) commuting activities, (B) leisure time activities, (C) household activities, and (D) activities at work and school.

▪ Sedentary behavior during leisure time will be measured with a subscale of the Activity Questionnaire for Adolescents & Adults (AQUA) [41].

▪ Smoking behavior: Smoking every day/smoking now and then/never smoked/year of smoking cessation and pack years (average number packs of 20 cigarettes per day smoked, multiplied by the number of years as a smoker).

▪ Determinants of behavioral change: A 41-item questionnaire, based on existing TPB questionnaires, will be used to assess lifestyle-specific behavior with regard to the constructs attitude, social norm, self-efficacy and intention to change. To our knowledge, no suitable validated questionnaires are available. The theoretical model and questionnaires in other current studies at the research institute were used to develop this Determinants of Lifestyle Behavior Questionnaire (DLBQ).

▪ Quality of life will be assessed with the EuroQol (EQ-5D) [42,42,43].

▪ Compliance: The number of CBP sessions attended will be registered, and compliance is considered adequate if at least two sessions are attended.

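### Number of sessions attended, a compliance measure that arises after randomisation, is listed as an adjustment factor for the outcome, which conflicts with the promised intention-to-treat analysis

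*Protocol article*

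**What the plan says.** The Analyses section of the protocol article sets the principle: "The analyses will be conducted according to the intention to treat principle". A few sentences later it gives a conditional rule: "If there are any relevant differences in baseline measurements between the two groups, we will adjust the outcome for these factors". The factors follow in brackets: "i.e. age, gender, ethnicity, BMI at the start of study, level of education, depression, smoking, number of sessions attended". The list opens with i.e., so it names the factors rather than giving examples.

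The Questionnaires section, under compliance, explains the last item: "The number of CBP sessions attended will be registered, and compliance is considered adequate if at least two sessions are attended". The Intervention group section says that the programme "will consist of a maximum of 6 individual 30-minute counseling sessions". The Control group section offers no sessions: "The participants in the control group will receive written information about their risk of developing T2DM and CVD, and existing brochures".

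The Analyses section also announces separate analyses of effect modifiers and mediators, but it does not assign sessions attended to them.

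**The concern.** Seven of the eight listed factors can be measured before randomisation. The eighth cannot. Attendance is a consequence of allocation, and the programme is offered in one arm only. The control value of zero is not stated word for word, but it follows from the Intervention group and Control group sections.

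Three things are at stake if the item enters the outcome model. First, attendance lies on the path through which counselling is meant to work, so conditioning on it can remove the effect the trial was set up to measure. Second, attendance is chosen by the participant, so conditioning on it can bring back confounding that randomisation had removed. Third, a variable that is zero in one whole arm is strongly correlated with arm, so precision falls even when there is no bias. The rule sits in the paragraph that governs every outcome, including both primary risk scores.

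**Working it through.** The plan states no figure on this point, so there is none to reproduce. The check has an algebraic part and a simulated part.

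**Inputs from the protocol (Sample size and Intervention group sections).** 300 participants per arm; at most 6 sessions; for the SD, "the standard deviation of the ARIC score was found to be 8.11"; a planning difference of 5, read here as 5 absolute points.

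**Assumed inputs (not in the protocol).** Three attendance distributions in the CBP arm, as probabilities of 0, 1, ..., 6 sessions:
- low: .15, .20, .20, .15, .10, .10, .10 (mean 2.55)
- middle: .10, .10, .10, .15, .15, .20, .20 (mean 3.55)
- high: .05, .05, .05, .10, .15, .25, .35 (mean 4.40)

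In the confounded scenarios, a prognostic trait lowers the score by 2.5 points per SD of the trait and correlates 0.5 with the latent tendency to attend.

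**What the coefficient means.** Take the model outcome = a + b × arm + c × sessions. Sessions are zero in every control, so c is estimated within the CBP arm alone. With m the mean number of sessions in that arm,

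b = (CBP mean − c × m) − control mean = ITT difference − c × m.

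This is the contrast extrapolated to zero sessions. If a total effect of -5 is proportional to sessions, c = -5/m and b = -5 − (-5/m) × m = 0, whatever m is.

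**Loss of precision.** With n per arm and v the variance of sessions in the CBP arm, the variance of the arm coefficient rises from 2σ²/n to (σ²/n)(2 + m²/v), a ratio of 1 + m²/(2v).
- low: v = 10.05 − 2.55² = 3.55; ratio = 1 + 6.50/7.10 = 1.9
- middle: v = 16.45 − 3.55² = 3.85; ratio = 1 + 12.60/7.70 = 2.6
- high: v = 22.40 − 4.40² = 3.04; ratio = 1 + 19.36/6.08 = 4.2

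The unadjusted SE is 8.11 × √(2/300) = 0.66. The adjusted SE is 0.66 × √1.9 = 0.92 at low attendance and 0.66 × √4.2 = 1.36 at high attendance.

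**Simulation.** 1,500 replicates per scenario, ordinary least squares, with no clustering and no other covariates. Estimates with sessions in the model are listed as low / middle / high attendance, with the two-sided 5% rejection rate in brackets.

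| True effect and attendance | Arm only | Arm + sessions |
|---|---|---|
| -5, proportional to sessions; unconfounded | about -5.0 (1.00) | -0.05 / 0.00 / +0.06 (0.05 / 0.04 / 0.05) |
| -5, proportional to sessions; confounded | about -5.0 (1.00) | +1.59 / +2.13 / +2.86 (0.41 / 0.51 / 0.56) |
| -5, unrelated to sessions; unconfounded | about -5.0 (1.00) | -5.01 / -5.01 / -5.03 (1.00 / 1.00 / 0.96) |
| -5, unrelated to sessions; confounded | about -5.0 (1.00) | -3.41 / -2.85 / -2.17 (0.96 / 0.76 / 0.34) |
| 0; unconfounded | about 0 (0.05 to 0.06) | +0.03 / 0.00 / -0.05 (0.06 / 0.05 / 0.04) |
| 0; confounded | about 0 (0.05 to 0.06) | +1.62 / +2.12 / +2.87 (0.42 / 0.50 / 0.57) |

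The direction of the confounded shift follows from the assumption that better-prognosis participants attend more. The opposite link would shift the estimate the other way.

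**The case against.** The strongest objection is that the adjustment may never happen. The rule applies only to relevant differences in baseline measurements, and sessions attended has no baseline value. A reader might infer that the item always triggers adjustment because the arms differ on it by design. The text does not support that: read literally, the item can never meet the condition. What stands is a contradiction. The condition excludes the variable and the list includes it, so an analyst working from the list would find on this item a difference guaranteed by design.

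A reader might also infer that the intention-to-treat estimate is lost. The text does not say so. It promises between-group differences in change with 95% confidence intervals before it reaches the conditional sentence, so an unadjusted comparison may well be reported too. The section does not say which result has priority.

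A third tempting reading is that a true effect would be erased. That happens when the whole benefit runs linearly through sessions, and there the zero follows by construction. If benefit is unrelated to sessions and attendance is unconfounded, the estimate survives and only precision suffers. Nor should the adjusted coefficient be read as the causal effect of being allocated to the programme and attending nothing. It has that meaning only if attendance is unconfounded and the model is right.

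Finally, the item may have been meant for the mediator analyses. That is possible, but the text places it in the outcome adjustment list and nowhere moves it.

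**Conclusion.** Wrong as written. A post-randomisation compliance measure that is zero in all controls is listed as an adjustment factor for the outcome, against both the rule's own baseline condition and the intention-to-treat commitment in the same section. This rests on the text alone, apart from the inference that controls attend no sessions.

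The size of the consequence is conditional. It rests on assumed attendance (mean 2.6 to 4.4 of 6 sessions), an assumed link between attendance and prognosis in the confounded scenarios, the protocol's ARIC SD of 8.11, a 5-point effect where one exists, and a simple model without clustering. Across those scenarios, the damage ranges from a variance 1.9 to 4.2 times as large with no bias, through a partly or wholly removed effect, to a reversed sign or a false-rejection rate of 42-57%. None of the scenarios with a true effect gains from the adjustment.

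**What to change.** Delete number of sessions attended from the adjustment list in the Analyses section, for all between-group analyses. Keep the variable for describing compliance, as the Questionnaires section already provides. If a question about dose or mechanism is wanted, put it in a separately labelled secondary compliance or mediator analysis with its assumptions stated; the mediator analyses already announced are a natural place.

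The cost is one phrase. No extra data are needed, the sample size does not change, and attendance is registered in any case.
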